### Assignment of interventions

#### Allocation

Consent and baseline measures will be collected prior to randomization to minimize reporting and selection bias. When the individual has completed the *diamond* CPT, he or she will be randomly assigned in a 1:1 ratio to the intervention or comparison arm. Randomization will be stratified by general practice and depressive symptom severity group. The allocation sequence will be computer-generated sequentially within stratum using a biased-coin algorithm [64] embedded within the Target-D website which is housed on the secure National eResearch Collaboration Tools and Resources (Nectar) cloud which provides computing infrastructure to Australian researchers. Using restricted randomization within the stratum ensures that number of individuals is balanced between study arms within stratum and the stratification factors will be balanced in each study arm. The randomization will be triggered automatically within the Target-D website, after a participant has completed baseline measurements and the *diamond* CPT, thus ensuring allocation concealment.

#### Blinding

Due to the nature of the intervention, participants cannot be blinded to their treatment allocation. However, GPs will not be notified of their patients’ allocation to either intervention or comparison arm. No emergency unblinding of GPs is anticipated, including in the case of the research team alerting the GP to patient suicidality. As outcome assessment is conducted online, no blinding of outcome assessors is required. All study analyses will be conducted by a statistician blind to participants’ allocation; study arm allocation will be coded as A or B, with the code for the study arm revealed only after data are analyzed.

### Data collection

Participant data will be collected from intervention and comparison arms using validated questionnaires on the Target-D website at screening, baseline and three and 12 months (Fig. 2). *diamond* CPT data will also be collected on the Target-D website. Participants will receive an automated email from the website at 80 and 358 days after *diamond* CPT completion with a unique link to the three-month and 12-month survey, respectively. Participants will be informed that if they decide to withdraw from the study, the data already provided will be retained and used in the analyses unless they request otherwise.

**Fig. 2 Fig2:**
[figure not shown]
Schedule of enrolment, interventions and assessments. *PHQ-9 *Patient Health Questionnaire – 9; *GAD-7* Generalized Anxiety Disorder scale; *MHSES* Mental Health Self-Efficacy Scale; *AQoL-8D* Assessment of Quality of Life scale; *MBS* Medicare Benefits Schedule; *PBS* Pharmaceutical Benefits Scheme

### Measures

Demographic characteristics, including age, gender, highest level of education, and employment status, will be assessed at baseline.

#### Primary outcome

Depressive symptom severity will be assessed at each timepoint using the PHQ-9. The PHQ-9 assesses the nine DSM symptoms of depression over the last two weeks using a 4-point Likert scale (where 0 = “not at all” and 3 = “nearly every day”). Total scores are in the range of 0–27, with suggested cut points of 5, 10, and 15 indicating mild, moderate, and severe depression, respectively [40]. The PHQ-9 is a validated diagnostic measure in primary care [65], with demonstrated efficacy and sensitivity as an outcome measure for treatment trials with a recommended Reliable Change Index [51].

#### Secondary outcomes

Self-efficacy will be measured using the Mental Health Self-Efficacy Scale (MHSES) [66]. The MHSES comprises six items that require respondents to rate on a 10-point Likert scale how confident they are in performing behaviors related to mental health self-care (from 1 = “not at all confident” to 10 = “totally confident”). Total scores are in the range of 6–60 and provide a unidimensional measure of self-efficacy; higher scores indicate greater levels of self-efficacy. The MHSES displays high internal consistency (Cronbach’s alpha = 0.91) and good construct validity, correlating well with measures of depression, anxiety, and functional impairment.

The seven-item Generalized Anxiety Disorder scale (GAD-7) will be used to assess anxiety [67]. The GAD-7 assesses the presence of anxiety symptoms over the past two weeks using a 4-point Likert scale. Scoring is similar to the PHQ-9; each item is scored from 0 to 3 (for a total possible score of 0–21), with cut points of 5, 10, and 15 corresponding to mild, moderate, and severe anxiety symptoms. The GAD-7 has excellent internal consistency (Cronbach’s alpha = 0.92) and test–retest reliability. Its construct, convergent, and discriminant validity are high; it correlates well with measures of depression and functioning (while assessing a distinct construct), as well as with other measures of anxiety.

Quality of life will be assessed at each time point using the Assessment of Quality of Life (AQoL-8D) [68]. This is a validated, reliable measure [69] that comprises eight dimensions (independent living, senses, pain, mental health, happiness, self-worth, coping, and relationships) that can be used to calculate quality-adjusted life years (QALYs) via a utility algorithm. The AQoL-8D has been shown to be sensitive to depressive symptom severity levels [69].

Cost-effectiveness of the intervention will be measured through assessment of health service use, effects on productivity, and calculation of QALYs. Health service use will be tracked using data extracted from the Australian Government Department of Health: the Medicare Benefits Schedule (MBS) that maintains information about visits to healthcare providers and diagnostic tests; and the Pharmaceutical Benefits Scheme (PBS) database of medications supplied on prescription. Participants will provide additional consent to access their MBS and PBS data. Other resource use not captured by these national databases, including the use of broader health and welfare services and effects on productivity (i.e. education and workforce participation), will be assessed via self-report using an adapted questionnaire developed by members of the research team and used in numerous other Australian mental-health intervention trials [70–72].

### Process data

To complement the outcome data collected as part of the RCT, a parallel process evaluation will be conducted in order to understand the context in which the outcomes were achieved. The evaluation will identify challenges of implementation and provide important guidance for future translation of trial findings, using the framework set out by the Medical Research Council [73]. The process evaluation will draw from data collected through a variety of sources, including but not limited to recruitment logbooks, interviews and surveys of GP and practice staff, intervention uptake and adherence data (as described above), and interviews with randomly selected participants (across both the two study arms and three depressive symptom severity groups). A comprehensive protocol for this evaluation will be published separately.

### Retention

To encourage retention at each study time point, non-responders will receive up to five reminders in total via phone, text, and email. These reminders will also provide the option of completing the baseline, three-month, or 12-month survey over the phone with an RA or being mailed a hard copy of the questionnaire to complete and return via reply paid envelope. At three and 12 months, participants who still do not complete the survey will be offered the option of completing the primary outcome measure (PHQ-9) alone. Outcome assessments may be completed in multiple sittings, with participants provided the option of saving their responses and returning later via a link emailed to them upon exiting the survey.

To acknowledge the time spent by participants and to further promote retention at three and 12 months, random draws for a $100 gift card will be conducted monthly for each follow-up survey, with all participants who completed the survey in the previous month eligible to receive a gift card. The selected participant will be contacted via phone and email. Participants will be advised of the draw in the initial email with their unique link to the relevant survey and in subsequent reminders.

### Data management

Participants will enter data directly into the Target-D website, which will store responses coded according to standard practice for each validated questionnaire. The website presents each item on a separate page to minimize the chance of items inadvertently being missed. Data integrity will be enforced through the use of forced or multiple choice items wherever possible; valid value and range checks will also be built into the website for free text fields where appropriate.

The coded study data will be downloaded weekly from the Target-D website, stored securely, and backed up regularly on a central password-protected University system. A data manager will check all data to identify and, where possible, resolve errors prior to analyses being conducted. Data will be kept for 15 years after study completion after which time they will be destroyed in accordance with University protocol [74].

The Research Electronic Data Capture (REDCap) secure software application [75] will be used to manage contact with participants and track progress through the study, with participant information transferred manually into REDCap from the Target-D study website. Both REDCap and the Target-D website are password-protected and housed on secure University servers; only the study team will have access to the identified data.

### Statistical methods

Descriptive statistics will be used to compare participant characteristics between the study arms, in total and stratified according to depressive symptom severity group. Linear mixed-effects model using restricted maximum likelihood with random intercepts for individuals will be used to estimate the difference in mean outcome between study arms at three and 12 months. All regression models will adjust for baseline outcome measure (where appropriate), stratification factors (practice, depressive symptom severity group) and time (baseline, three and 12 months), with a two-way interaction between study arm and time except baseline where means in the study arms will be constrained to be equal. Baseline variables strongly associated with the outcome that are found to be imbalanced between the study arms will also be considered for adjustment in the regression analyses. Estimated intervention effects will be reported as the difference in the means of the outcome between study arms (intervention-comparison), with 95% confidence intervals and *p* values. Similar regression analyses will also be used to compare the outcomes between intervention and comparison arms separately for each of the three depressive symptom severity groups. In a secondary analysis, we will investigate the intervention effect on individuals who would comply with their assigned treatment using a complier average casual effect (CACE) analysis [76]. A detailed analysis plan will be developed for the secondary and sensitivity analyses. All analyses will be performed using Stata 13.0 [77].

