#### Primary outcome

The primary outcome is the difference between the two treatment arms in mean depressive symptom severity at three months, controlling for baseline depressive symptom severity. Depressive symptom severity was selected as the outcome measure rather than a clinical diagnosis of major depressive disorder as it is more relevant to the design and delivery of stepped mental healthcare.

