### Sample size

Sample size calculation was based upon our trial experience, a systematic review of depression trials [55] and current data from the *diamond* study [39]. The primary objective is to test for a standardized effect size of 0.2SD in mean depressive symptoms at three months between the intervention and comparison arms. However, we based our calculations on our planned subgroup analyses because the sample size required would need to be larger to test for difference between study arms within each of the three depressive symptom severity groups than combined. Therefore, we based sample size on detecting a standardized mean difference of 0.2 between arms for the minimal/mild group (given the potential floor effect we anticipate a smaller intervention effect). We hypothesized a standardized effect size of 0.5 in the moderate and severe depressive symptom severity groups as they have room for greater improvement and will receive more intensive treatments.

Based on the CPT development work, we anticipated that 70% of participants will be classified as being likely to have minimal/mild depressive symptoms, 15% as moderate, and 15% as severe depressive symptoms at three months. We used these estimates to extrapolate the total sample size needed to ensure that we had sufficient power for the sub-group analyses. Based on these assumptions, we required 158 (78 in each arm) participants in each of the moderate and severe groups to detect a standardized effect size of 0.5 and 740 (370 in each arm) in the mild/minimal group to detect a smaller standardized effect size of 0.2, with 80% power and 5% significance level for a two-sided test.

This leads to an anticipated sample size of 1056 participants (528 in each arm), which is also sufficient for the primary objective to detect a standardized effect size of 0.2 in the mean PHQ-9 between study arms, with 90% power and 5% significance level. A standardized effect size of 0.2 is equivalent to a mean change of 1.35 points in the mean depressive symptoms assuming a standard deviation on 6.75 (based on *diamond* data). This effect size is in keeping with those found in systematic reviews of interventions to decrease depressive symptom severity in primary care [57].

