We inflated the required sample size to 1320 to allow for 20% attrition at 12 months. Based upon documented response rates and depressive symptom prevalence gathered from our experience of recruiting participants with depressive symptoms in the primary care setting [39], achieving this sample size at baseline requires that we invite 22,000 adults to complete the screening tool (Fig. 1).

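### Read literally, the primary mixed model uses baseline PHQ-9 twice, as covariate and as outcome row, which would make the three-month standard error too small; the text should fix one use of baseline and a covariance to match

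*Protocol article*

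**What the plan says.** The Statistical methods section of the protocol article gives one model for all mean comparisons: a linear mixed model fitted by REML, with a random intercept for each individual and no other covariance structure named. On covariates it says "All regression models will adjust for baseline outcome measure (where appropriate), stratification factors (practice, depressive symptom severity group) and time", where the first item carries the hedge and time is listed with three levels, baseline among them. The arm-by-time interaction applies at every time "except baseline where means in the study arms will be constrained to be equal". Similar models are to be run within each severity group. The section defers a detailed plan only for the secondary and sensitivity analyses, so this is the stated primary model.

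The Primary outcome section defines the comparison as "mean depressive symptom severity at three months, controlling for baseline depressive symptom severity". The Sample size section sets the standard that the test must meet: "to detect a standardized effect size of 0.2 in the mean PHQ-9 between study arms, with 90% power and 5% significance level". The test is described as two-sided for the subgroup calculation in the same section.

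**The concern.** There are two standard ways to use a baseline measurement. In one, baseline is a covariate and only the follow-up values are outcomes. In the other, baseline is itself an outcome row and the arm means are set equal there (the constrained longitudinal model). Either controls for baseline. The sentence in Statistical methods takes elements of both.

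If both are applied, the covariate at the baseline rows is the response itself, so little residual variation is left in those rows. A model with one residual variance and one random intercept pools those small residuals with the follow-up residuals. It then understates the variance of the three-month outcome and reports an interval that is too narrow and a p value that is too small. At stake is the 5% level of the primary test, and of every other comparison of an outcome measured at baseline.

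**Working it through.** **The plan's own figures.** For 0.2 SD, 90% power and two-sided 5%: 2 × (1.960 + 1.282)² / 0.2² = 525.4, so 526 per arm. The planned 528 per arm gives 90.1% power; 1056 / 0.8 = 1320; 0.2 × 6.75 = 1.35. The sample size for the primary comparison reproduces. The question is whether the stated analysis delivers the 5% on which it rests.

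**Inputs.** From the Sample size section: N = 1056, 1:1, SD 6.75 (variance S² = 45.56), severity groups 70/15/15%. From Statistical methods: REML, random intercept only, arm terms at 3 and 12 months only. Not in the article, hence assumed: correlations between time points, and any baseline SD other than 6.75.

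**Hand check of the literal model.** Take SD 6.75 at all times, all correlations 0.5, and no stratification factors.

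1. With a random intercept, the single baseline slope is the regression of the person's mean over three times on baseline: (1 + 0.5 + 0.5)/3 = 2/3.
2. Residual variance at baseline: (1 − 2/3)² S² = 5.06. At follow-up: [(0.5 − 2/3)² + 0.75] S² = 35.44.
3. Residual covariances: baseline with each follow-up, (1/3)(−1/6) S² = −2.53; between follow-ups, [(1/6)² + 0.25] S² = 12.66.
4. The fitted model has one variance, (5.06 + 2 × 35.44)/3 = 25.31, and one covariance, (−2 × 2.53 + 12.66)/3 = 2.53. Its weight on the baseline row is k = 2.53/25.31 = 0.10.
5. Variance the model believes: 25.31 − 2.53²/25.31 = 25.06, so SE = √(4 × 25.06/1056) = 0.308.
6. Actual variance: 35.44 + 2 × 0.10 × 2.53 + 0.10² × 5.06 = 35.99, so SE = √(4 × 35.99/1056) = 0.369.
7. Ratio 0.308/0.369 = 0.834. Type I error 2Φ(−1.96 × 0.834) = 10.2%; coverage of the 95% interval is about 90%.

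For comparison, an ANCOVA at three months has variance 0.75 S² = 34.17 and SE 0.360, correctly estimated.

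**Other settings, literal model.**

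| Check under no effect | Model SE / true SE | Type I error, 3 months |
|---|---|---|
| Large-sample grid, 120 settings of correlation and baseline SD | 0.78 to 0.895 | 7.9 to 12.6%, median 10.4% |
| Simulation, 1,500 trials per setting, severity group and 14 practices (assumed number) | 0.82 to 0.88 | 8.8 to 10.7% |
| Simulation with severity group, further settings | 0.81 to 0.86 | 8.7 to 10.6% |
| 1320 recruited, 15% and 20% missing at 3 and 12 months, 181 runs | 0.83 | 12.7% (Monte Carlo error about 2.5 points) |

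Inflation appeared in every setting of the grid. At 12 months the grid gave 9.5 to 14.1%.

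**Remedies.**

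- Follow-up rows only, baseline as covariate: 3.7 to 4.8% in one set of simulations and 3.8 to 5.0% in another.
- Constrained model, covariate deleted, random intercept kept: 3.9 to 4.9% with SD 6.75 throughout and no stratification factors. With severity group and practice, 5.3 to 7.4%; with severity group in settings that include a smaller baseline SD, 6.6 to 9.3%.

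The second result can also be seen by hand. Take baseline SD 4.5, follow-up SD 6.75, correlations 0.5 (baseline with 3 months), 0.4 (baseline with 12) and 0.6 (3 with 12), and no covariates. The pooled variance is (20.25 + 45.56 + 45.56)/3 = 37.13 and the pooled covariance is (15.19 + 12.15 + 27.34)/3 = 18.23, so k = 0.491. The model believes 37.13 − 18.23²/37.13 = 28.18. The actual variance is 45.56 − 2 × 0.491 × 15.19 + 0.491² × 20.25 = 35.53. The SE ratio is √(28.18/35.53) = 0.891 and the type I error is 8.1%, with baseline used only once.

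**The case against.** The strongest reply is that the hedge on the baseline covariate already covers this: constraining the arms at baseline is itself an adjustment, so the covariate is not appropriate where baseline is an outcome row. That reading is possible, and it stands to this extent: the article does not prove that the analyst will fit the double-use model. But the more natural meaning is that the adjustment applies where the outcome has a baseline value, as PHQ-9 has. Since the section gives baseline as a time level for all models, the benign reading leaves the covariate little to apply to. The wording does not settle between a valid and an invalid analysis.

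A reader might take the Primary outcome section as proof of double use, since it speaks of controlling for baseline severity. It is not: either method satisfies that phrase.

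A reader might also blame the whole inflation on the duplicated covariate. Part of it comes from elsewhere: a single residual variance when baseline and follow-up SDs differ, and a severity group that enters with the same effect at all times although it is derived partly from baseline PHQ-9 (Background). Deleting the covariate does not remove that part.

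That a later analysis plan could clarify the matter is true of any text. It is not a full answer here, because this article states the primary model itself.

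**Conclusion.** The concern holds as a defect in a stated rule, conditional on the literal reading. Under that reading the three-month standard error is about 12 to 20% too small (10 to 22% at the extremes of the grid), and the type I error is about 8 to 13% against the planned 5%. The direction was the same in every setting of the grid. The exact size depends on correlations and a baseline SD that the article does not give.

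Two stronger conclusions are not supported. The treatment estimate is not biased, because randomisation protects it; only its standard error, interval and p value are affected. And no single inflation figure can be attached to this trial as fact, both because the hedge leaves a valid reading open and because the inputs are assumed. It should still be corrected, since it concerns the primary p value and the correction is nearly free.

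**What to change.** Use baseline once, and say how.

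- **Preferred.** Keep only the 3- and 12-month values as outcome rows. Enter the baseline outcome as a covariate with a slope allowed to differ by time, together with practice and severity group. Remove baseline from the levels of time and drop the equal-means constraint.
- **Alternative.** Keep baseline, 3 and 12 months as outcome rows with equal arm means at baseline. Delete the baseline outcome from the covariates for every outcome measured at baseline, replace the random intercept by an unstructured residual covariance, and add severity-group-by-time terms. The unstructured covariance lets the variance differ by time, and the added terms let the effect of severity group do so; the random-intercept version forces both to be constant. This version was not itself simulated here.

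Apply the same choice to the secondary outcomes and to the analyses within severity groups, where the group terms drop out.

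The cost is a few sentences in Statistical methods and matching analysis code, made before the A/B code is opened. No data or participants are needed. Under the preferred form, participants with neither follow-up contribute no rows; the planned sensitivity analysis for missing data should cover them.

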Therefore, we developed a novel prognostic model using data from the *diamond* cohort study [39] to predict depressive symptom severity at three months [38]. It comprises 17 items assessing depressive symptom severity at baseline as measured by the Patient Health Questionnaire-9 (PHQ-9) [40]: sex; current anxiety; history of depression; presence of chronic illness affecting daily functioning; self-rated health; living alone; and perceived ability to manage on available income. Based on an individual’s score, he or she is stratified into one of three groups based on predicted depressive symptom scores at three months; namely, minimal/mild (those predicted to have a PHQ score of ≤ 10 at three months), moderate (PHQ > 10 and < 13), and severe (≥13). Cutoffs for the three groups were established during the development of the *diamond* CPT and are explained in full elsewhere [38]. In the intervention being tested in the current study, individuals are then:Presented with feedback reflecting their responses to the CPT;Provided an opportunity to set priorities and reflect on motivation to change; andPresented with an evidence-based treatment recommendation matched to group classification.

The presentation of feedback and treatment recommendation was informed by the principles of motivational interviewing [41] and an iterative development process employing user-centered design principles to ensure the information is presented in a way that is meaningful and engaging for participants [42].

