##### Severe depressive symptoms at three months

The severe group will be offered collaborative care, an enhanced form of patient care shown to be effective for treatment of moderate to severe depression in primary care [21, 52–54]. Collaborative care is defined as including four key ingredients: a multi-professional approach to patient care; a structured management plan; scheduled follow-ups; and coordinated communication between health professionals involved in management [21, 55]. Target-D participants involved in collaborative care will receive eight appointments with a trained case manager (CM). The CM role will be filled by a non-mental-health specialist such as a registered nurse. This decision was made as it is in keeping with the role filled by practice nurses in managing other chronic conditions such as diabetes and thus should enhance scalability of the Target-D model of care should it be effective.

The Target-D approach to collaborative care is underpinned by the principles of motivational interviewing, to enhance patient engagement and action. The Target-D CM will receive training in the intervention approach by a qualified psychologist and will receive regular supervision and support from the psychologist and project manager (SF) throughout the trial.

Patients in this group will be reminded of upcoming appointments with the Target-D CM via SMS. After each appointment, patients will receive an email from their CM summarizing their discussion and outlining the actions the patient intends to take to manage his/her mental health. With the patient’s consent, the CM will also send a copy of this email to the treating GP and other professionals involved in the patient’s mental healthcare.

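### The pooled primary model holds the severity-group gap constant over time, so the three-month estimate can shift slightly if outcome dropout differs by arm within severity group

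*Protocol article*

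**What the plan says.** Statistical methods gives the primary analysis: "Linear mixed-effects model using restricted maximum likelihood with random intercepts for individuals will be used" to estimate the arm difference at three and 12 months. Baseline is itself a response occasion, since arm by time applies "except baseline where means in the study arms will be constrained to be equal". The adjustment terms are "stratification factors (practice, depressive symptom severity group) and time (baseline, three and 12 months), with a two-way interaction between study arm and time", and no other interaction is named. A later detailed plan is promised only for secondary and sensitivity analyses, so the primary model is fixed in this text.

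The severity groups come from the prediction tool. Background and rationale says of the prognostic model: "It comprises 17 items assessing depressive symptom severity at baseline as measured by the Patient Health Questionnaire-9 (PHQ-9", followed by sex, anxiety, depression history, chronic illness, self-rated health, living alone and income. The groups are cut on the predicted three-month score: minimal/mild up to 10, then "moderate (PHQ > 10 and < 13), and severe (≥13".

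Under Sample size, "we anticipated that 70% of participants will be classified as being likely to have minimal/mild depressive symptoms, 15% as moderate, and 15% as severe". That section hypothesises effects of 0.2 SD in minimal/mild and 0.5 SD in moderate and severe, and allows for 20% attrition at 12 months without a split by arm or severity.

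**The concern.** With severity group as a main effect only, the fitted severe-minus-mild difference is one number shared by baseline, three and 12 months. Groups formed partly from the baseline score tend to look further apart at baseline than later. If so, the common gap is too wide at three months.

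This does no harm while both arms keep the same severity mix. It matters if outcome loss changes the mix in one arm and not the other, because the model then corrects for the changed mix with the wrong gap, and the error goes into the primary three-month contrast. The design leaves room for such a pattern. In the intervention arm, contact runs from automated emails for the minimal/mild group to the severe group, where "Target-D participants involved in collaborative care will receive eight appointments with a trained case manager (CM". The comparison arm receives the same attention contact whatever the group.

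**Working it through.** **1. The plan's own figures.** Target: 0.2 × 6.75 = 1.35 points. Per arm at 90% power, two-sided 5%: 2 × (1.960 + 1.282)² / 0.2² ≈ 526. The planned 528 per arm gives power 0.901, and 1056 / 0.8 = 1320. These reproduce and set the scale for what follows.

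**2. The model as written.** For group g, time t, arm A and practice p:

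mean = μ(t) + γ(g) + π(p) + δ(t) × A, with δ(baseline) = 0.

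The severity gap γ(severe) − γ(mild) does not depend on t. The alternative replaces γ(g) with γ(g,t).

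**3. Is a constant gap plausible?**
- Selection on baseline PHQ-9 makes shrinkage likely. The documents give no group means, so its size has to be assumed.
- The plan's own effects also narrow the gap. Applying the overall SD of 6.75 to each group (an assumption), (0.5 − 0.2) × 6.75 = 2.0 points in the intervention arm, or about 1.0 averaged over arms.

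**4. How bias arises.** Roughly, shift ≈ Σ over groups of (fitted gap − true three-month gap) × (group's retained share in comparison − retained share in intervention). If dropout differs by arm alone or by severity alone, the share differences are zero and so is the shift.

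Hand example, using the first simulated setting below. Shares are 70/21.6/8.4%, the severe gap goes from 12.9 to 7.5 and the moderate gap from 7.7 to 4.4. Comparison dropout is 20% throughout; intervention dropout is 20/30/40%.
- Intervention retained: 0.70 × 0.8 = 0.560; 0.216 × 0.7 = 0.151; 0.084 × 0.6 = 0.050; total 0.762.
- Retained shares: moderate 19.9%, severe 6.6%. Differences from comparison: 0.0175 and 0.0178.
- With the fitted gap taken as midway, the excess is (12.9 − 7.5)/2 = 2.7 for severe and (7.7 − 4.4)/2 = 1.65 for moderate.
- Shift ≈ 2.7 × 0.0178 + 1.65 × 0.0175 = 0.08. Simulation, which also accounts for within-person correlation, gives 0.095.

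**5. Simulation of the stated model.** REML, random intercept, baseline arm means equal, practice omitted, 500,000 participants per setting, groups cut at predicted scores of 10 and 13. Assumed, not in the documents: baseline SD 5.5 to 6, slope of three-month on baseline PHQ-9 0.45 to 0.7, SD of the other predictors 1.2 to 2.5, and all dropout patterns. Entries are the three-month estimate with group as a main effect minus the estimate with group by time. Benefit is negative, so a positive shift is towards no effect. Dropout is listed as mild/moderate/severe.

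| Severe − mild gap, baseline to 3 months | Comparison 20/20/20, intervention 20/30/40 | Comparison 15/30/40, intervention 20/20/20 | Extreme: comparison 20/20/20, intervention 20/50/60 |
|---|---|---|---|
| 12.9 to 7.5 | +0.095 | −0.126 | +0.263 |
| 11.5 to 8.8 | +0.055 | −0.070 | +0.146 |
| 11.6 to 10.0 | +0.037 | −0.046 | +0.093 |
| 12.5 to 11.2 | +0.033 | −0.041 | +0.083 |
| 11.2 to 10.9 | +0.004 | −0.004 | +0.009 |

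As a share of the target, the largest moderate shift is 0.126 / 1.35 = 9.3% and the largest extreme shift is 0.263 / 1.35 = 19.5%. With no dropout or 20% in every cell, the shift is 0.00.

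**6. A separate refit** of the same random-intercept model assumed gaps of 10.7, 7.4 and 6.7 at the three occasions and a constant effect. Intervention dropout of 20/25/30% against 20% gave +0.04; 20/30/40% against 15% gave +0.08; 20/30/45% against 15% gave +0.10. Better retention of severe intervention participants gave −0.03.

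**7. Effects that differ by group.** With no regression at all (gap 9.5 at both times) and a constant effect, the shift is 0.00. With the hypothesised 0.2/0.5/0.5 SD effects it is +0.03 for intervention 20/30/40% against 20%, and −0.04 for intervention 20% against comparison 15/30/40%.

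**8. Precision.** Adding the term makes the model-based SE 0 to 3% smaller. The empirical SE is 0.366 against 0.366 with complete data at N = 1056. With 20% dropout it is 0.360 against 0.356, and in another setting at N = 1320 it is 0.345 against 0.345.

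**The case against.** The case against acting is substantial, and most of it limits the point rather than removing it.

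- **Shrinkage is not forced.** A reader might infer that the gap must narrow. The groups are cut on a predicted three-month score that uses several predictors besides PHQ-9, and one plausible setting goes only from 11.2 to 10.9. This stands.
- **The dropout pattern is not indicated.** Only an arm-by-severity difference in outcome loss does harm. Surveys go to everyone, with up to five reminders, phone or postal completion and a PHQ-9-only fallback in both arms. Stopping the programme is not the same as losing the outcome. This makes the large patterns less likely but does not exclude moderate ones.
- **The direction is unknown.** A reader might infer dilution of the effect. That holds only if the intervention arm loses more severe participants; case-manager contact could equally improve their retention, and then benefit is exaggerated.
- **Precision.** A reader might infer a meaningful loss of power. The empirical SE does not support that.
- **Larger shifts can be obtained** with an unstructured covariance: about 0.05, 0.11 and 0.17 in the three patterns of step 6. The protocol states random intercepts, so those figures do not describe its model.
- **Missing-at-random protection is not simply lost.** Baseline PHQ-9 stays in the model as a response and carries part of the severity information, and a missing-data sensitivity analysis is promised. No content is given for that analysis, so it cannot be counted on to catch an error in the mean model.
- **The baseline clause.** "All regression models will adjust for baseline outcome measure (where appropriate") might be read as a repair. It does not say how baseline could be a covariate when it is already a response, so it settles nothing.

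**Conclusion.** The point holds as a modest specification weakness in the primary model. A severity gap that is constant over time is an unsafe assumption given how the groups are formed and the effects the trial expects. It biases the three-month estimate only when outcome dropout differs by arm within severity group.

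The size is about 0 to 0.13 points in moderate patterns, in either direction, and up to about 0.26 in an extreme one. The largest moderate shift is 0.126 / 0.2995 = 0.42 of the model-based standard error in that setting with 20% dropout in every cell. It will rarely change the conclusion, but it sits in the primary estimate and comes from a variable recorded for every participant. All sizes rest on assumed gaps, correlations and dropout, because the documents give none of these by group. Only PHQ-9 was examined. The documents do not support a claim of certain bias, bias in a known direction or a material loss of power.

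**What to change.** In Statistical methods, state the fixed effects of the pooled PHQ-9 model as arm by time with baseline means constrained equal, severity group by time, and practice. Use the same form in the other pooled outcome models for consistency.

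The cost is (3 − 1) × (3 − 1) = 4 parameters in a model with more than 1000 participants. In every dropout pattern simulated with a constant treatment effect, the added term brought the bias to about zero, within simulation error of about 0.02 points.

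It does not remove the reweighting that arises when true effects differ by severity group and the retained mix differs by arm. With the hypothesised 0.2/0.5/0.5 SD effects and the three dropout patterns of step 6, a large-sample calculation left 0.02 to 0.05 points with the term, against 0.05 to 0.14 without it. The models fitted separately within each severity group need no change.
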